Kines & Mikkelsen (2003) attempted to investigate rates of elevation fall injuries as a function of enterprise size in the Danish construction industry in the years 1993-1999 [18]. They used the following enterprise categorization: 0; 1-4; 5-9; 10-19; 20-49; 50-99; and > = 100 employees, yet their results were inconclusive; no noticeable trend was found. But as was noted by the authors, the investigation was possibly biased due to an underreporting of approximately 50% of the injuries. Moreover, enterprise size was not given in 13% of the reported injuries. Another problem with the study was that there was no control for the occupational distribution within the enterprises. According to Danish national data, injury rates among blue collar workers are on average twice as high as they are among white collar workers [19]. Also, it has been shown that injury rates differ between occupational categories among blue collar construction workers [20].

In contrast, three studies do indicate a trend of decreasing injury rates with enterprise size in the construction industry valid for the following settings: Ontario, Canada in the years 1988 to 1993 [21], South Korea in the years 1991 to 1994 [22], and Italy in the years 1995 to 2000 [8]. None of these three studies controlled for occupational distribution within the enterprises; hence, at least part of the decline in injury rates might be due to an increasing proportion of white-collar employees in the larger enterprises.

The primary aim of the present study is to investigate the relation between enterprise size and injury rates in the Danish construction industry, on a data set that is free from reporting bias, while controlling for the occupational distribution within the enterprises. A conditional aim will be to examine if there is an association between a change in Danish legislation and injury rates among construction workers in enterprises with 5-9 employees. The change, which was implemented from July 1, 2002, cancelled the requirement to have a safety organisation for enterprises with 5 - 9 employees and may have resulted in a higher risk of injury in these enterprises.

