### Statistical analyses

A person will become a case once receiving a principal diagnosis in the ICD-10 interval S00-T98 ("injury, poisoning and certain other consequences of external causes") according to the OHR. For any given calendar year, a person will be censored at the time he becomes a case, emigrates or dies. Time-dependent dummy variables are used to categorise the manual workers into micro enterprises (fewer than 5 employees), small enterprises (5-9 employees), medium-sized enterprises (10-19 employees), and large enterprises (20 or more employees). A person's work category during a certain calendar year is determined by his enterprise association according to the population census performed in the end of November the preceding year.

The null hypothesis stating that "the injury rates among workers are independent of enterprise size" will be tested. If this first null hypothesis is rejected meaning that the observed injury rates most likely depend on enterprise size, a second null hypothesis will be tested. This second null hypothesis will test if "the relative rate of injury among workers in enterprises with 5-9 employees compared with other workers is independent of time period (January 1, 1999 - June 30, 2002 versus July 1, 2002 - December 31, 2005)". By this, it shall be tested if it can be assumed that the legislative change that took place in Denmark on 1 July, 2002, which cancelled the requirement of having a safety organisation in enterprises with 5 - 9 employees, did not have any effect on the injury rates among the workers in enterprises with 5-9 employees.

To deal with intra-enterprise correlations, a multi-level Poisson regression will be used to model the outcome, where the enterprises will be treated as the subjects while observations within the enterprises will be treated as correlated repeated measurements.

The analyses will be controlled for age (five-year age groups), calendar year (as categorical variable) and occupation. Occupation unit groups are: Bricklayers and stonemasons (DISCO-88 = 7122); Carpenters and joiners (DISCO-88 = 7124); Plumbers and pipe fitters (DISCO-88 = 7136); Electricians (DISCO-88 = 7137); Painters and wall-paper workers (DISCO-88 = 7141); Unskilled manual workers in construction workers (DISCO-88 = 9313).

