The analyses will be performed by use of the GENMOD procedure in SAS version 9.1. Only main effects will be considered. The empiric standard error estimates will be used and an exchangeable correlation structure is assumed. The significance level will be set to 0.05. Table 1 shows the rate ratios and 95% confidence intervals that will be calculated.

**Table 1 T1:** Manual construction workers' relative risk rates of injury, by enterprise size and type of profession

	Injury Rate Ratio	Confidence Interval (95% CI)

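### The analyses are limited to main effects, but the second null hypothesis is a size-by-period interaction, so the legislative-change aim cannot be answered by the model as written

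*Protocol article*

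**What the plan says.** All references are to the protocol article.

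- **Aim.** The Background announces the second question: "A conditional aim will be to examine if there is an association between a change in Danish legislation and injury rates among construction workers", specifically in enterprises with 5-9 employees.
- **Hypothesis 2.** In Statistical analyses, once the hypothesis of no relation between size and injury rate has been rejected, "a second null hypothesis will be tested". It is that "the relative rate of injury among workers in enterprises with 5-9 employees compared with other workers is independent of time period", with the periods given as "January 1, 1999 - June 30, 2002 versus July 1, 2002 - December 31, 2005".
- **Model.** A Poisson regression clustered on enterprise is to be fitted in SAS GENMOD. Its terms are enterprise size class, age group, calendar year as a categorical variable, and occupation. The section then states: "Only main effects will be considered".
- **Output.** "Table 1 shows the rate ratios and 95% confidence intervals that will be calculated". Its rows are three size contrasts against large enterprises and six occupation contrasts against other manual workers. No row refers to a period.

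**The concern.** Hypothesis 2 asks whether an effect of enterprise size changed on a given date. In a log-linear rate model this is a product term, and the main-effects sentence excludes product terms. An analyst who follows that sentence cannot carry out a test that the same section declares.

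At stake is the only analysis that addresses the removal of the safety-organisation requirement for enterprises with 5-9 employees. Any effect of the law would be averaged into the overall small-versus-large rate ratio, and no estimate or interval for the change itself would be produced.

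**Working it through.** **Nothing to reproduce.** The article gives no sample size, event count or numerical power for this test. The point is structural.

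**Step 1: the model as written.** With the listed terms,

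log(rate) = a + b(size) + c(year) + d(age) + e(occupation).

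For workers of the same age group, occupation and year, the log rate ratio of small enterprises to any other class k is b(small) - b(k). It contains no period term. The ratio of rate ratios (RRR, later period over earlier) is therefore exp(0) = 1 by construction.

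**Step 2: could another stated term carry the effect?**

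- The size variables are described thus: "Time-dependent dummy variables are used to categorise the manual workers into micro enterprises (fewer than 5 employees), small enterprises (5-9 employees". Time-dependence here means that a worker's class is updated each year from the preceding November census. It does not let the effect of a class differ between periods.
- Calendar year is a main effect. It shifts the rates of all size classes by the same factor.
- No period variable, period-stratified fit or separate model for hypothesis 2 is described.

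**Step 3: numerical illustration.** Poisson models with a person-years offset were fitted to expected counts. All inputs are assumptions, since the article gives none:

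- person-years per year of 30,000 (micro), 20,000 (small), 20,000 (medium) and 30,000 (large);
- a base rate of 0.10 per person-year;
- rate ratios against large of 1.20, 1.10 and 1.05 for micro, small and medium before the change;
- follow-up 1999-2005, with 2002 split at 1 July;
- a true RRR applied to small enterprises from that date.

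| True RRR | Main-effects model: small vs large, before / after | Fitted RRR | RRR with size-by-period term added |
|---|---|---|---|
| 1.00 | 1.100 / 1.100 | 1.00 | 1.00 |
| 1.10 | 1.155 / 1.155 | 1.00 | 1.10 |
| 1.25 | 1.2375 / 1.2375 | 1.00 | 1.25 |
| 1.50 | 1.375 / 1.375 | 1.00 | 1.50 |

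The middle column can be checked by hand. With constant yearly person-time and two windows of 3.5 years, the fitted small-versus-large ratio is 1.10 × (1 + RRR)/2. For RRR = 1.25 this is 1.10 × 1.125 = 1.2375. Adding a main effect of period leaves the fitted RRR at 1.00; only the product term recovers it. The averaged ratios depend on the assumed inputs. The fitted RRR of 1.00 does not.

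**Step 4: the windows.** 1 January 1999 to 30 June 2002 is 1,277 days, and 1 July 2002 to 31 December 2005 is 1,280 days. The study period in Methods/Design runs to 31 December 2006, which would make the later window 1,645 days. The article does not say why hypothesis 2 stops a year earlier, so any wording for its model has to state which end date applies.

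**The case against.** The best reply is that the main-effects sentence was meant for the primary model. It stands just before Table 1, which concerns size and profession only, while hypothesis 2 is set out as its own later test with its own comparator and dated periods. A specific provision can be read as qualifying a general one. The hypothesis could also be tested without a product term, by fitting the main-effects model in each period and comparing the two rate ratios. And in a journal article, a missing table row for a conditional test is weak evidence by itself.

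Part of this stands. The authors may well have intended a separate model, and a main-effects route by period exists. But the sentence covers the analyses without exception, and neither route is described. The article does more than leave a detail to a fuller document: it states a rule that excludes the needed term.

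A reader might infer four further faults, which the article does not support:

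- **That the testing order is a defect.** The article declares the aim conditional, in the sentence that opens "If this first null hypothesis is rejected meaning that the observed injury rates most likely depend on enterprise size, a second null hypothesis will be". Ordered testing is a legitimate choice, and dropping it is a trade-off. One can imagine a small-enterprise ratio below 1 before the law and above 1 after it, averaging to about 1 and blocking the second test. But hypothesis 1 concerns all size classes, and Table 1 has one P value for the whole size factor. The second test would be blocked only if micro and medium enterprises also resembled large ones.
- **That categorical calendar year prevents a cut in mid-2002.** Calendar year is a control variable. Hypothesis 2 defines its periods by date, and cases are censored at the time of injury, so follow-up can be split at 1 July.
- **That the plan will treat non-rejection as proof of no effect.** The wording about what can be assumed is awkward, but it can be read as a paraphrase of the null hypothesis. No such decision rule is given.
- **That the primary analysis is compromised.** It is not; hypothesis 1 needs main effects only.

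**Conclusion.** The point holds for the conditional second aim and no further. Followed literally, with a single model over both periods, the plan fixes the quantity of interest at a ratio of rate ratios of 1 and plans no estimate of it. This follows from the model form and needs no assumption about rates or numbers. It does rest on reading the main-effects sentence as written, for all analyses. If the authors meant it for hypothesis 1 alone, the correction is one of wording, but it is still needed, because the model for hypothesis 2 is then nowhere stated. Hypothesis 1 and every contrast in Table 1 remain testable as planned.

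**What to change.** 1. Limit the main-effects sentence to hypothesis 1.
2. Add for hypothesis 2, for example: *The model for hypothesis 2 adds period (before, or from, 1 July 2002) and the product of period with the indicator for 5-9 employees. Person-time in 2002 is split at 1 July. Follow-up for this model ends on 31 December 2005.* If 2006 is to be included instead, say so and reconcile the stated window with the study end of 31 December 2006.
3. Add a row to Table 1 for the ratio of rate ratios (later over earlier period, 5-9 employees versus other workers) with its 95% confidence interval.
4. State that a non-significant result will be interpreted through that interval.

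The conditional order of testing can stay as declared. The cost is a few sentences, one table row and one further model run, with no new data.

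### The plan allows main effects only, but the second hypothesis is a size-by-period interaction, so the specified model cannot test the effect of the 2002 legislation

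*Protocol article*

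**What the plan says.** All references are to the protocol article.

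- **Aim.** The Background section states: "A conditional aim will be to examine if there is an association between a change in Danish legislation and injury rates among construction workers", with enterprises of 5-9 employees as the class concerned. The change took effect on 1 July 2002.
- **Hypothesis.** Under Statistical analyses, if independence of injury rate and enterprise size is rejected, "a second null hypothesis will be tested". Its content is that "the relative rate of injury among workers in enterprises with 5-9 employees compared with other workers is independent of time period", with the periods given as "January 1, 1999 - June 30, 2002 versus July 1, 2002 - December 31, 2005".
- **Model.** In the same section, "a multi-level Poisson regression will be used to model the outcome". Size enters as dummy variables for the four classes. "The analyses will be controlled for age (five-year age groups), calendar year (as categorical variable) and occupation".
- **Restriction.** The closing paragraph of that section, which names the SAS procedure, the standard errors and the correlation structure, adds: "Only main effects will be considered". The sentence before it refers to the analyses in general, and nothing exempts the second hypothesis.
- **Planned output.** Table 1 lists rate ratios for size (three classes against large) and for occupation (six groups against other manual workers). It has no period-specific ratio and no ratio of rate ratios.

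**The concern.** A statement that a relative rate does not depend on period is a statement about an interaction. A main-effects model assumes that statement to be true and cannot test it. A main effect of period would not help, because it would show whether the rate of all workers changed, not whether the 5-9 class changed relative to the rest.

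At stake is the study's only evaluation of a change in law. An analyst who follows the text has nothing to report for it. An analyst who wants to report something must depart from the text. Because the second test is run only if the first null hypothesis is rejected, the form of that departure (product term, separate fits by period, choice of comparison group in the model) would be settled when the first result is already known.

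**Working it through.** The article states no figure for this point, so there is none to reproduce. The check is algebraic, followed by an illustration on assumed inputs.

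**1. What the specified model implies.** With the listed terms,

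log(rate) = intercept + size + age group + calendar year + occupation.

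For two workers of the same age group and occupation in the same year, the log rate ratio of the 5-9 class against another class *k* is

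size(5-9) − size(*k*).

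It contains no time term. The rate ratio before 1 July 2002 therefore equals the rate ratio after it, and the ratio of the two is fixed at 1.

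**2. What the hypothesis needs.** Let S = 1 for the 5-9 class and P = 1 from 1 July 2002. Add δ·P + γ·(S×P) to the model. The change in the log relative rate of the 5-9 class against other workers is then γ, and the second null hypothesis is γ = 0. The main-effects rule deletes γ.

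**3. What the main-effects model returns instead.** Assume constant person-time in each class, a constant rate in other workers, and a true relative rate *r*(t) in the 5-9 class. Let p be the share of person-time in that class, R the single fitted ratio and r̄ the time-average of *r*(t). With calendar-year effects fitted, the Poisson score equation for the 5-9 indicator becomes

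r̄ × (1 − p + pR) = R × (1 − p + p r̄), which gives R = r̄.

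The fitted ratio is the time-average. Under these assumptions it does not depend on p; the numerical fit used p = 20%.

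Lengths from the stated dates: 42 months in each hypothesis window, and 96 months for the whole study period (1999 to 2006), of which 96 − 42 = 54 fall after the change.

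| True ratio before → after | Fitted, 42 + 42 months | Fitted, 42 + 54 months |
|---|---|---|
| 1.00 → 1.10 | (42×1.00 + 42×1.10)/84 = 1.050 | (42×1.00 + 54×1.10)/96 = 1.056 |
| 1.00 → 1.20 | (42×1.00 + 42×1.20)/84 = 1.100 | (42×1.00 + 54×1.20)/96 = 1.1125 |

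**4. A second numerical check with all four classes.** Assumed inputs: base rate 0.15; rate ratios 1.2, 1.1, 1.05 and 1.0 for micro, small, medium-sized and large; 30,000, 20,000, 20,000 and 40,000 person-years per year; follow-up 1999 to 2005 with 2002 split at mid-year. The Poisson model was fitted to expected counts, first with main effects only and then with period and the product term added.

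| True ratio of rate ratios | Main effects: small vs large, before / after | Ratio implied | With product term |
|---|---|---|---|
| 1.0 | 1.100 / 1.100 | 1.00 | 1.00 |
| 1.1 | 1.155 / 1.155 | 1.00 | 1.10 |
| 1.3 | 1.265 / 1.265 | 1.00 | 1.30 |

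The main-effects values are again averages: 1.1 × (1 + 1.1)/2 = 1.155 and 1.1 × (1 + 1.3)/2 = 1.265. The product term recovers the assumed change each time.

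**5. Whether another part of the text supplies the test.** It does not. The time-dependent dummies update which size class a worker belongs to, and do not let the effect of a class differ by period. Categorical calendar year is shared by all classes. No stratified fit is described, and Table 1 has no row for the comparison.

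**The case against.** The best defence is that the sentence was meant only for the model behind Table 1. It stands in the paragraph that introduces that table, and every row of the table is a main effect. The second hypothesis is set out separately, with its contrast, dates and trigger, and a specific commitment would normally override a general modelling remark. This reading is plausible, but the text does not state it: the restriction applies to the analyses as a whole and follows both hypotheses.

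A second defence is that the question remains answerable. Main-effects models could be fitted separately by period and the two ratios compared, or a dummy could be added for 5-9 employees from July 2002. Both would work, although the dummy is an interaction under another name. This limits the finding to the model as specified; the data could answer the question. Neither route is written down.

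Three further points stand in part:

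- The contrast, cut date, windows and gatekeeping condition are fixed in advance, so the freedom left to the analyst concerns the form of the test, not the choice of hypothesis.
- The second hypothesis is conditional, and the first does not depend on it.
- The numerical illustration rests on assumed inputs and adds nothing to the algebra beyond a sense of scale.

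That this is a condensed article does not settle the matter. A missing detail could be left to a fuller plan, but here a stated rule excludes a stated hypothesis.

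**Conclusion.** The concern holds. The hypothesis and the modelling rule in the same section contradict each other. Followed literally, the plan gives no test statistic and no estimate for the legislation question. The relative rate is forced to be equal in both periods whatever the true change, and any real change is absorbed into the average effect of the 5-9 class. The conclusion follows from the form of the model and needs no assumption. Only the illustrative sizes (1.05 or 1.056 returned for a true change from 1.00 to 1.10) depend on assumed person-time and rates, which the article does not give. The first hypothesis and the estimates in Table 1 can be analysed as planned. The contradiction should be removed before analysis, because as written a declared hypothesis cannot be tested.

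**What to change.** Limit the restriction and name the missing term. Suggested text:

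*Only main effects will be included in the model for the first hypothesis and Table 1. The second hypothesis will be tested by adding period (before / from 1 July 2002) and the product of the 5-9 employee indicator and period, with the size-class terms retained. The result will be reported as a ratio of rate ratios with a 95% confidence interval based on the empirical standard errors.*

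Two details should be carried over explicitly from the hypothesis as it stands:

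- The test uses the two stated windows. The second ends on 31 December 2005, although the study period runs through 2006. If 2006 is meant to be included, the hypothesis must say so.
- Follow-up in 2002 must be split at 1 July. In every other year period is determined by calendar year, so with year fitted as a categorical variable the main effect of period is estimated from within 2002 only. The product term is still estimable from all years.

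A row for this ratio should be added to Table 1 or to a separate table. The cost is one sentence in the plan, one extra model for the second test and a split of one year's person-time. No new data are needed.

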**Enterprise size in construction (P = xxxx)**		

**Micro vs. large**		

**Small vs. large**		

**Medium-sized vs. large**		

**Type of construction profession (P = xxxx)**		

**Bricklayers and stonemasons vs. other manual construction workers**		

**Carpenters and joiners vs. other manual construction workers**		

**Plumbers and pipe fitters vs. other manual construction workers**		

**Electricians vs. other manual construction workers**		

**Painters and wall-paper workers vs. other manual construction workers**		

**Unskilled construction workers vs. other manual construction workers**		

## Discussion

Since this is not a randomized study, we cannot rule out that selection into the enterprises may influence the estimates in the sense that cautious people, for example, might prefer employment in large enterprises where safety more often seems to be a priority and different regulatory requirements for safety leads to fewer risk situations. Whereas more reckless people who care less about the potential dangers, or may thrive better with their own risk perception as they themselves decide when to take precautions relative to safety, might prefer employment in small enterprises where fewer legal requirements for safe work must be respected. The effect of enterprise size would then be intensified by the effect of personality type and would bias the estimates away from unity. Conversely, a selection bias towards unity would be the case if, for example, an owner of a micro enterprise focuses on avoiding human and economic losses caused by work-related injuries and therefore is carefully seeking to recruit diligent workers. Moreover, workers in a micro enterprise are probably in closer contact to the management (or owner) compared with those working in a large enterprise and such a close proximity would make it easier for the management to detect risky behaviour in the workplace and dismiss it before injuries occur. We believe, however, that our study group is far more homogeneous than those in most other occupational risk studies and this may counteract potential selection bias. All of the included workers are manual workers belonging to the same industry and most of them are belonging to the same occupational class (skilled workers). The exception is the occupational group 'unskilled construction workers', but this will be controlled for in the analysis.

The Occupational Hospitalisation Register is free of reporting bias. All hospital contacts are registered, and there are virtually no missing principal diagnoses. This can be contrasted with two alternative national data sources held by the Danish Working Environment Authority and the National Board of Industrial Injuries, respectively, to whom merely 45% of all work-related injuries are reported [30]. Another advantage of the study is that we have identification numbers on the people as well as the enterprises, which enables us to take intra-enterprise correlations into account. Since the local workplace unit number is based on each geographically bounded production unit, this study provides more precise information about workplace size than the mother company number which merely sums up the number of employed for all subordinated workplaces. The study is further strengthened by its sample size, which will afford sufficient statistical power to the various hypothesis tests.

A disadvantage of the Occupational Hospitalisation Register is that it leaves out injuries that do not need hospital treatment. Another disadvantage is that we have annual but not daily information about occupation and enterprise. Enterprise association at the time of the injury might be different from the enterprise association in the end of November the preceding calendar year and the occupational category might change during the course of the year. We believe that most of the occupational categories are quite stable since we are dealing with skilled workers. It would, for example, be unlikely that a trained carpenter would shift into a brick layer trainee in the course of a calendar year. The construction industry is, however, known for its high turnover rate [31]. Within a calendar year, a worker in a small enterprise might, for example, move to a large enterprise, where he is injured. According to our model, such an injury would erroneously be classified as having happened in a small enterprise. The size of an enterprise may also change during a calendar year. All such changes would bias our estimates toward unity; from this perspective, the estimates should be regarded as conservative. As such, we hope that our study will contribute to a better assessment of relative injury rates in small and medium-sized enterprises.

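### With four enterprise-size classes, misclassification does not always bias the ratios toward unity, so small and medium-sized vs large cannot be called conservative without conditions

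*Protocol article*

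**What the plan says.** Under Statistical analyses, the protocol article sorts manual workers into four size classes: fewer than 5, 5–9, 10–19, and 20 or more employees. Size is measured once a year, at the November census before the follow-up year (the rule begins "A person's work category during a certain calendar year is determined by his enterprise association according to the population census performed in the end of"). Table 1 plans three separate size ratios: "Micro vs. large", "Small vs. large" and "Medium-sized vs. large".

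The Discussion admits that this record may be out of date when an injury occurs. It says "The construction industry is, however, known for its high turnover rate", gives the example of a worker who moves from a small to a large enterprise and is injured there, and adds that an enterprise may itself change size during the year. It concludes: "All such changes would bias our estimates toward unity; from this perspective, the estimates should be regarded as conservative". No condition is attached on who moves where, or on how risk varies with size.

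**The concern.** Non-differential error in a two-class exposure pulls the ratio toward 1, and the Discussion's single example is of that kind. With four classes, the small and medium-sized groups each lie between two others. If a neighbouring class has a higher rate, its person-time raises the recorded rate of the intermediate class. A ratio that is truly 1 can then depart from 1, and a modest true ratio can be overstated.

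This bears on how two of the three size ratios in Table 1 are read. A reader told in advance that every estimate is conservative would take an apparent excess in the 5–9 class as a lower bound, when part or all of it could be risk carried in from micro enterprises.

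**Working it through.** **Inputs from the article.** There are four classes, large is the reference, and class is fixed from the preceding November. The article gives no bias figure to reproduce, and no true ratios, class shares or movement rates. Those are assumed below. For scale only, the Background's European incidence rates give 6,500 / 4,700 = 1.38 for SMEs vs large.

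**Formula.** Let s_j be the true share of class j, P(i|j) the probability that class j is recorded as i, and r_j the true rate relative to large. The expected recorded rate in class i is

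R_i = Σ_j s_j P(i|j) r_j / Σ_j s_j P(i|j), and the observed ratio is R_i / R_large.

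**Assumed set-up.** Shares are 30/20/20/30% (micro/small/medium/large). The same fraction of each class is misclassified, with 60% or 80% of the errors going to adjacent classes and the rest to non-adjacent ones, split equally in each case.

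**One case in full.** Take 20% error, 80% of it adjacent, and true ratios 1.5/1/1/1.
- Recorded small: 0.048 from micro, 0.160 from small, 0.016 from medium, 0.006 from large; total 0.230. R = 1 + 0.5 × 0.048/0.230 = 1.104.
- Recorded large: 0.006 from micro, 0.008 from small, 0.016 from medium, 0.240 from large; total 0.270. R = 1 + 0.5 × 0.006/0.270 = 1.011.
- Small vs large: 1.104 / 1.011 = 1.09, where the truth is 1.00.

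**Over 10–30% error and both adjacency settings:**

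| True micro/small/medium | Observed micro | Observed small | Observed medium |
|---|---|---|---|
| 1.5 / 1.0 / 1.0 | 1.34–1.47 | 1.03–1.13 | 1.00–1.01 |
| 1.5 / 1.1 / 1.02 (monotone, convex) | 1.34–1.47 | 1.11–1.18 | about 1.02 |
| 1.5 / 1.33 / 1.16 (near-linear) | 1.33–1.46 | 1.24–1.32 | 1.08–1.14 |
| 1.0 / 1.0 / 1.0 | 1.00 | 1.00 | 1.00 |

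In the first two rows small vs large moves away from 1 while micro vs large is attenuated. In the third row every ratio is attenuated, as the article says.

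**Medium-sized vs large.** Suppose the excess lies in micro and small only (1.4/1.4/1.0), and a recorded medium-sized worker spends 10% of his time in each neighbouring class. Recorded medium is 0.1 × 1.4 + 0.8 × 1 + 0.1 × 1 = 1.04. Large draws only on medium and large, so it stays at 1.00. The ratio is 1.04 instead of 1.00.

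**Two classes against four.** Mixing patterns were drawn at random, with 70–95% correctly classified and true ratios spanning 1.0–1.5. None of 100,000 two-class draws moved away from 1. With four classes and a monotone gradient, the ratio lay farther above 1 than the truth in 0% of draws for micro, 3.4% for small and 19.3% for medium. These shares depend on the assumed ranges. They show that the effect exists, not how likely it is here.

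**Limits for micro vs large.** Without monotonicity, about 14% of draws moved micro vs large farther from 1 or across it. Movement out of construction also matters. Assume 5/5/10/20% of time (micro to large) is spent in outside jobs at half the large-class rate, with true ratios 1.40/1.20/1.10. Micro is then (0.95 × 1.40 + 0.05 × 0.5) / (0.80 + 0.20 × 0.5) = 1.355 / 0.90 = 1.51.

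**Before/after contrast for 5–9 vs other workers.** With the same mixing and true ratios in both periods, the bias cancels: 1.00 stays 1.00. With 20% error, a true change of 1.10 is seen as about 1.06. If error rises from 20% to 30% between periods and nothing else changes, a false change of 1.04–1.05 appears (true 1.5/1/1/1).

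**The case against.** The sentence is a remark on limitations. It fixes no model, test or contrast, and the same paragraph discloses the November lag, the turnover and the changes in enterprise size. The largest distortions above come from a chosen shape, with all the excess in micro; near-linear gradients support the article. All of this stands. It limits the point to interpretation and shows that no specific amount of bias can be claimed for this study.

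Three stronger readings are tempting, and the documents support none of them.
- A reader might infer that small and medium-sized vs large will be inflated. The direction depends on mobility and gradient, and the article gives neither.
- A reader might infer a false rejection of the first null hypothesis. If rates are equal in all classes, non-differential movement among them leaves every ratio at 1.
- A reader might infer that the legislation test is undermined because it concerns the 5–9 class. That test compares periods, so a constant bias cancels. A false change needs mobility or the neighbouring classes' rates to change between periods, and nothing in the article shows that they do.

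Nor should the claim for micro vs large be kept without conditions. The Background reports lower European rates at 1–9 than at 10–49 employees, so a monotone gradient cannot be taken for granted.

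**Conclusion.** The unconditional statement is wrong as written for a four-class exposure, since one valid counterexample refutes a claim about all changes and all estimates. The direction of bias for small and medium-sized vs large is indeterminate. Under the assumed inputs, small vs large moves from 1.00 to about 1.03–1.13, and the one medium-sized example moves from 1.00 to 1.04; other plausible inputs attenuate every ratio. Micro vs large is expected to be attenuated only if the gradient is monotone and movement is non-differential and confined to the four classes. The planned Poisson model stands. So does the test of the overall null, for movement among the four classes. What changes is what may be concluded from two of the three size ratios. Whether such a distortion would reach significance cannot be settled, because the article gives no worker or injury counts.

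**What to change.** 1. Delete the sentence that calls all estimates conservative.
2. In its place, state that micro vs large is expected to be attenuated if injury rates are monotone in enterprise size and movement is non-differential and within the four classes. State also that the direction of bias for small and medium-sized vs large is indeterminate without data on movement.
3. Add a supporting sensitivity analysis restricted to workers in the same size class at the two preceding November censuses, for follow-up years in which both exist. Registration of all local workplace units began only at the start of the study period, so the earliest years may drop out.
4. Optionally, repeat the analysis with follow-up in January–March only, closest to the census.

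Do not make interpretation of the intermediate classes depend on agreement between these analyses; no criterion for agreement is defined.

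The cost is a change of wording and one or two re-runs on subsets of records the study already plans to link. Report the drawbacks: both analyses have wider intervals, the first selects stable workers, and the second covers a single season.
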